### Objectives and outcomes

The primary objectives are to estimate the prevalence of low V_T_ ventilation (V_T_ < 8mL/kg of PBW) in the first 24 hours of spontaneous ventilation in patients with hypoxemic ARF and its association with ventilator-free days on day 28. Tidal volume will be assessed five times over the first 24 hours after the transition to spontaneous ventilation to account for potential variation. To determine whether V_T_ was below or above 8 mL/kg of PBW for a given patient, we will calculate the weighted average V_T_ based on the duration of each evaluation period. Accordingly, the first assessment, collected one hour after the transition, carries a weight of 1/24, the second assessment, collected 5 hours after (and 6 hours after the transition), carries a weight of 5/24, and the third, fourth and fifth assessments, collected after 12 hours, 18 hours and 24 hours of the transition, respectively, will each carry a weight of 6/24.

The secondary objectives are to estimate the association between the rate of adherence to low V_T_ ventilation in spontaneous ventilation and survival, estimate the incidence of asynchrony in the first 24 hours after the transition to spontaneous ventilation and associated mortality, estimate the proportion of patients who returned to sedation and controlled MV in the first 24 hours or at any time after the transition to spontaneous ventilation, assess the adherence to low positive end-expiratory pressure (PEEP) by fraction of inspired oxygen (FiO_2_) table in the first 24 hours after the transition to spontaneous ventilation, and identify barriers associated with nonadherence to low V_T_ ventilation during spontaneous ventilation.

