### Study measures and data collection

The following baseline characteristics related to admission to the ICU and initiation of MV will be obtained from the patient's medical records: age, sex, height (assessed using a tape measure with the patient in the supine position), weight reported by the ICU team, main reason for admission to the ICU, cause of ARF, arterial oxygen pressure/fraction of inspired oxygen ratio (PaO_2_/FiO_2_) on the day of the ARF diagnosis, date of intubation, risk factors for ARDS, comorbidities (cardiac, respiratory, neurological, renal, hepatic, immunosuppression, cancer, arterial hypertension, diabetes and smoking) and Simplified Acute Physiology Score 3 (SAPS 3). We will calculate the PBW according to the following formulas:

$$\begin{array}{c} 50+0.91\times \left(\text{height in centimeters}-\;152.4\right)\text{for males}\\ 45.5+0.91\times \left(\text{height in centimeters}-\;152.4\right)\text{for females} \end{array}$$

We will also retrospectively collect the ventilatory parameters from the day before inclusion in the study from the patient's medical records, in addition to the use of vasopressors, sedatives, neuromuscular blockers and analgesics, ARDS diagnosis, Richmond Agitation-Sedation Scale (RASS) score, presence of *delirium* assessed by the Confusion Assessment Method in an Intensive Care Unit (CAM-ICU) scale or clinical assessment, Sepsis-related Organ Failure (SOFA) score, blood gas analysis and other laboratory data for diagnosing organ failure. We will also calculate the respiratory system compliance and resistance from the day before study enrollment (for patients under deep sedation and/or neuromuscular blockage). The main study measures and data collection methods are shown in table 2.

**Table 2 t2:** Characteristics of the study population

Characteristic		Value
Age (years)		xx ± x
Male, n (%)		n (xx)
BMI (kg/m^2^)		xx ± x
SAPS 3 score		xx ± x
SOFA		xx (xx - xx)
LIP score		xx (xx - xx)
Charlson index		xx (xx - xx)
Cause ARF		
	Pneumonia (bacterial, viral, opportunistic)	n (xx)
	Extrapulmonary sepsis	n (xx)
	Coma/lowered level of consciousness	n (xx)
	Cardiogenic pulmonary edema/heart failure	n (xx)
	Aspiration	n (xx)
	Hypovolemic shock	n (xx)
	Others	n (xx)
Days of intubation prior to inclusion		xx (xx - xx)
Cause of hospitalization		
	Acute respiratory failure	n (xx)
	Sepsis	n (xx)
	Neurologic diseases	n (xx)
	Postoperative monitoring	n (xx)
PaO_2_/FiO_2_ ratio at ARF diagnosis		xx ± x

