### One hour before transition

The following data on controlled ventilation will be recorded retrospectively: ventilatory mode; programmed respiratory rate; patient's total respiratory rate; minute ventilation; peak airway pressure; V_T_; and PEEP. We will also collect vital data (heart rate, mean arterial pressure, peripheral oxygen saturation), arterial blood gas analysis data (obtained as close as possible to the collection of ventilatory data will be recorded), the presence of major asynchronies,^(23)^ the use of vasopressors, the use of sedatives and analgesics, the RASS score, the presence of *delirium* assessed by the CAM-ICU scale or clinical assessment.

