The comparison of V_T_ during the initial 24 hours of spontaneous ventilation (less than 8mL/kg of PBW versus greater than 8mL/kg) in relation to ventilator-free days within 28 days will be performed using mixed generalized regression models considering the distribution that best fits the data, incorporating center as a random effect. We constructed a conceptual causal diagram in the format of a directed acyclic graph (DAG),^(24)^ including the association between V_T_ during the first 24 hours of spontaneous ventilation and ventilator-free days at 28 days and the most relevant variables (Figure 1S - Supplementary Material): body mass index (BMI) and SAPS 3 at baseline, SOFA on the day before transition, PaO_2_/FiO_2_ at the moment of the ARF diagnosis, and PEEP, RASS, and pH one hour before transition.

All analyses will be performed using the R statistical program (R Core Team; Vienna, Austria; https://www.R-project.org), and we will consider p < 0.05 to indicate statistical significance.

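### The variables named for the primary analysis of tidal volume and ventilator-free days take oxygenation only from ARF diagnosis and leave out prior ventilation time, although a pre-transition blood gas and days of intubation are both collected

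*Protocol article*

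**What the plan says.** Under Objectives and outcomes, the primary objectives cover the prevalence of low tidal volume and "its association with ventilator-free days on day 28". Under Statistical plan analysis, this comparison uses a mixed generalized regression model with center as a random effect. The same paragraph continues: "We constructed a conceptual causal diagram in the format of a directed acyclic graph (DAG". It then names seven variables: BMI and SAPS 3 at baseline, SOFA on the day before transition, and "PaO_2_/FiO_2_ at the moment of the ARF diagnosis, and PEEP, RASS, and pH one hour before transition".

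The article also describes data that are collected but not in that list:

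- Study measures and data collection includes "date of intubation, risk factors for ARDS", and Table 2 has a row "Days of intubation prior to inclusion".
- For the day before inclusion, the same section lists "Sepsis-related Organ Failure (SOFA) score, blood gas analysis and other laboratory data for diagnosing organ failure".
- One hour before transition, the study records "arterial blood gas analysis data (obtained as close as possible to the collection of ventilatory data will be recorded". Table 3 has PaO2 and FiO2 rows with a column for that time point.

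Under Follow-up, the day of inclusion is day 0 for ventilator-free days.

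**The concern.** In an observational comparison, the credibility of the estimate rests largely on how well the groups are matched at the start of exposure. Here that start is the transition to spontaneous breathing, and the outcome clock starts on the same day.

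Two features of the patient at that moment could plausibly drive both the spontaneous tidal volume and the time to liberation: how impaired gas exchange then is, and how long the patient has already been ventilated. The article itself gives a mechanism for the second, since its Introduction links controlled ventilation to loss of diaphragm mass and to weakness. Ventilation days before inclusion are not part of the outcome, so nothing in the outcome definition accounts for them.

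The list takes PEEP, RASS and pH one hour before transition but oxygenation from diagnosis, and gives no reason for the difference. If the diagnosis value is a poor proxy for the state at transition, and prior ventilation is not held constant, part of any difference in ventilator-free days could reflect the patients' stage of illness and not their tidal volume.

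**Working it through.** **1. Timing and availability, side by side**

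| Variable | Time point named for the analysis | Nearest pre-transition value collected |
|---|---|---|
| PaO2/FiO2 | ARF diagnosis | One hour before transition (PaO2 and FiO2 in Table 3); blood gas on the day before inclusion |
| Days ventilated before inclusion | Not listed | Date of intubation; Table 2 row |
| SOFA | Day before transition | Same |
| PEEP, RASS, pH | One hour before transition | Same |

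Table 1 sets no maximum interval between ARF diagnosis and transition. The exclusion of tracheostomized patients probably limits very long intervals, but an interval of several days is compatible with the criteria. FiO2 is missing from the text list for one hour before transition but appears in Table 3 at that time point, so the ratio can be formed. Both additions precede the exposure, so neither can be a mediator.

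**2. The plan's own figures**

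- Prevalence: n = 1.96² × 0.5 × 0.5 / 0.05² = 384.1, and 384.1 × 1.10 = 422.6. This reproduces the stated 422.
- Power: 422 × 0.90 ≈ 380 evaluable, difference 3 days, SD 9, two-sided 5% (two-sided is assumed).
  - At 25% or 75% prevalence, SE = 9 × √(1/95 + 1/285) = 1.066 and power is 80.3%.
  - At 50% prevalence, SE = 9 × √(1/190 + 1/190) = 0.923 and power is 90.1%.

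The claim of at least 80% reproduces, and the point below does not change it.

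**3. Illustration for prior ventilation (inputs assumed, not in the document)**

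Bias = (ventilator-free days lost per prior ventilation day) × (difference in prior days between tidal volume groups that remains after the listed variables). Both terms must be conditional on those variables.

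- Low end: 0.1 × 1 = 0.1 day, or 0.1/3 = 3% of the target difference.
- High end: 0.5 × 3 = 1.5 days, or 1.5/3 = 50% of the target difference.

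**4. What a bias of given size would do to the test**

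With no true association, the rejection rate is Φ(b/SE − 1.96) + Φ(−b/SE − 1.96), using the standard errors from step 2.

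| Bias b | 25% prevalence | 50% prevalence |
|---|---|---|
| 0.5 day | 7.6% | 8.4% |
| 1.0 day | 15.5% | 19.1% |

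These rates use the unadjusted SD of 9 and ignore clustering by center. They show how sensitive the test is and do not predict what will happen.

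**The case against.** **The list is not stated to be the adjustment set.** The article calls these the diagram's most relevant variables and does not say that they are all the fixed effects of the model. The diagram is a supplementary figure that is not shown, and a fuller protocol or analysis plan may exist. A reader might infer that the model certainly omits these covariates, but the text does not go that far, and a reason drawn from the diagram cannot be excluded. This stands as a limit on certainty. It does not remove the point: a list with time points, placed beside the primary model, is a stated choice, and a diagram for this exposure and outcome has no other evident use.

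**Severity near transition is partly covered.** Four of the seven variables (SOFA, PEEP, RASS, pH) are measured at or near transition, and SOFA has a respiratory component. This also stands. It narrows the oxygenation gap without closing it, and none of the four measures ventilation history.

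**Sex.** A reader might count sex as a third omitted confounder because it enters the exposure through predicted body weight. At 160 cm, the weight is 50 + 0.91 × 7.6 = 56.9 kg for a man and 45.5 + 0.91 × 7.6 = 52.4 kg for a woman, so 450 mL is 7.9 and 8.6 mL/kg respectively. That shows a link to exposure only. No section links sex to ventilator-free days, and height enters the same formula. Adjusting for a variable that affects exposure but not outcome can cost precision and amplify remaining bias.

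**Conclusion.** The point holds for two variables. Among those named for the primary ventilator-free-days analysis, oxygenation is taken from an earlier time than necessary and ventilation time before inclusion is absent. Better pre-exposure data for both are collected. Some confounding by stage of illness is therefore left open that could be closed at almost no cost.

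The size and direction of the residual bias cannot be obtained from the document. The range of 0.1 to 1.5 days for prior ventilation rests entirely on an assumed 0.1 to 0.5 day lost per prior day and an assumed residual difference of 1 to 3 days. A reader might go further and add an oxygenation bias to a ventilation-history bias, concluding that a third to two thirds of the 3-day difference could be spurious. The documents do not support this. Such a sum needs group differences and slopes that they do not give. It also treats the two biases as acting in the same direction without overlap, and ignores what SOFA and PEEP already absorb.

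This is an improvement that should be made to a primary analysis. It is not proof that the analysis is materially confounded.

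**What to change.** In the fixed effects of the ventilator-free-days model, and in the causal diagram:

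1. Add the PaO2/FiO2 nearest before transition, beside or in place of the value at ARF diagnosis. Use the gas recorded for one hour before transition and otherwise the one from the day before. State that only samples drawn before transition count, so that the covariate stays pre-exposure.
2. Add days of invasive ventilation before inclusion, calculated from the date of intubation.
3. Handle missing blood gases by the same rule as for pH, which depends on the same kind of sample.

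If the diagram gives a reason to leave either variable out, state that reason instead. Sex may be added in a sensitivity analysis.

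The cost is two covariates with about 380 evaluable patients, so the loss of degrees of freedom is negligible. No new data collection is needed and the sample size of 422 is unaffected. The change should be fixed and dated before the association is analyzed.

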### Data collection and quality assessment

All data will be collected at each center by an investigator trained in an electronic case report form (CRF) developed in the Research Electronic Data Capture (RedCap) electronic database. The electronic database has its fields formatted to accept specific ranges of values for each variable, reducing the chances of entering incorrect values. The most important variables will be analyzed for missing, discrepant or inconsistent data. A backup copy of the database will be saved periodically and will be archived at the end of the study.

### Ethical aspects

The study was approved by the Research Ethics Committee of the *Hospital das Clínicas* of the *Universidade de São Paulo* (CAAE 28482720.0.1001.0068) and by the Ethics Committee of each participating institution, when needed. Informed consent was waived due to the observational nature of the study. The protocol is registered on the international platform ClinicalTrials.gov (NCT06042036). Each patient will be identified by a study number to protect confidentiality.

We will submit the study results for publication in accordance with the recommended guidelines for reporting observational studies, The Strengthening the Reporting of Observational Studies in Epidemiology (Strobe).^(25)^ The results of the primary study will be published in a peer-reviewed journal.

### Current status

The recruitment of participants started in June 2023, and we expect to complete this study by June 2024.

## DISCUSSION

The SPIRAL study was developed to describe the ventilation of patients with ARF in spontaneous ventilation, mainly with respect to the V_T_ applied in this phase. Randomized clinical trials have shown that low V_T_ and limited plateau pressure during controlled ventilation reduce mortality and ventilator-induced lung injury,^(3,7)^ and clinical practice guidelines recommend using protective ventilation, defined as a V_T_ of 4 - 8mL/kg and a plateau pressure below 30cmH_2_O.^(2,26)^ However, in spontaneous ventilation, the V_T_ varies according to the adjusted level of inspiratory assistance and the patient's inspiratory effort, which makes it difficult to control the V_T_. Previous physiological studies^(27,28)^ have shown that it is possible to maintain V_T_ below 8mL/kg of PBW in the majority of patients diagnosed with ARDS who are transitioning to spontaneous ventilation. The study's focus on adherence to low V_T_ during spontaneous ventilation reflects challenges faced by clinicians in daily practice. We chose to use a cutoff of 8mL/kg PBW instead of 6mL/kg because although most clinical randomized trials have targeted 6mL/kg PBW, V_T_ up to 8mL/kg were allowed in most studies.^(4,7)^ Additionally, clinical guidelines define protective ventilation as a V_T_ of 4 - 8 mL/kg^(2,26)^ and prior observational trials^(19)^ have used this definition.

The study's primary and secondary objectives cover a broad spectrum of clinical outcomes, including ventilator-free days, survival, incidence of asynchrony, and identification of potential barriers to adherence to low V_T_, enabling a comprehensive view of the impact of ventilation strategies on patient-centered outcomes. Data will be collected at several timepoints during the first 24 hours after the transition to spontaneous ventilation. This approach takes into account possible variations over time and will enable a differentiated understanding of V_T_ dynamics during this critical period. Due to possible variations in V_T_ with spontaneous ventilation over time, we chose to use the weighted average of V_T_ to obtain a more representative assessment of the ventilation dynamics during the first 24 hours of spontaneous ventilation.

The multicenter and multinational characteristics of our study, with the participation of ten Latin American countries, add significant diversity to the population of patients included and allow a more comprehensive understanding of regional variations in clinical practices. This observational study will reflect real-life clinical scenarios, and the findings will be derived from routine patient care settings, increasing the practical relevance of the results. This study has the potential to influence clinical decision-making, inform future clinical trials, and ultimately improve patient outcomes.

Our study has some limitations. We will collect detailed data regarding ventilatory parameters only for the first 24 hours of the transition to spontaneous ventilation, and we recognize that these first 24 hours are not necessarily representative of the remaining days in MV; in addition, patients can only be included once in the study because survival is one of the secondary outcomes; therefore, we will only collect data for the first transition. The tidal volume will not be obtained continuously but rather will be collected at several timepoints during the first 24 hours of spontaneous ventilation. To better represent these variations, we will calculate the weighted average of the V_T_ based on the duration of each evaluation period. This method takes into account changes in V_T_ over a 24-hour period, assigning different weights to each data point.

The participating ICUs in the study were invited using the databases of large research networks, and it is possible that the investigators in the ICUs had more knowledge and experience with MV than did the average Latin American ICU practitioners, which could generate selection bias and restrict the external validity of the study. However, invitations were sent to a large number of ICUs regardless of research experience, and we did not restrict participation to active network members. Although the multinational approach increases external validity, the specific regional characteristics of Latin American ICUs may limit the generalizability of the results to countries in other parts of the world.

In conclusion, this study may provide valuable contributions to understanding protective ventilation practices in patients with ARF during the transition to spontaneous ventilation in Latin American ICUs, especially after the COVID-19 pandemic. The results can potentially inform clinical practice and future clinical trials and impact the treatment of patients with acute respiratory failure.
